## Schedule in months

|                         | 1 | 2 | 3 | 4 | 5 | 6 | 7 | 8 | 9 | 10 | 11 | 12 | 13 | 14 | 15 | 16 | 17 | 18 | 19 | 20 | 21 | 22 | 23 | 24 |
|-------------------------|---|---|---|---|---|---|---|---|---|----|----|----|----|----|----|----|----|----|----|----|----|----|----|----|
| Execution               | x | x | x | x | x |   |   |   |   |    |    |    |    |    |    |    |    |    |    |    |    |    |    |    |
| Analysis                |   | x | x | x |   |   |   |   |   |    |    |    |    |    |    |    |    |    |    |    |    |    |    |    |
| Publication preparation |   |   | x | x | x |   |   |   |   |    |    |    |    |    |    |    |    |    |    |    |    |    |    |    |

## **Definition of the Problem**

Healthcare personnel have a high risk of COVID-19 infection (1). In China, until the beginning of March, more than 3300 COVID-19 infections in medical staff have been reported, and in some hospitals such as Clinic Barcelona 23% of physicians have contracted COVID-19. In Italy, the estimated incidence of COVID-19 is similar, with 20% of medical staff infected (1). Another severe problem is that healthcare workers may take the COVID-19 infection to their homes, having transmission to their family members been reported; besides, personnel might be an in-hospital vector, spreading the infection to patients being treated for other causes, or to the rest of the medical team.

Disease in healthcare personnel is an extremely severe problem in health emergencies, since it limits capacity of attention, weakens the workforce and diminishes motivation. In fact, in China 40,000 physicians were mobilized from other regions to support Wuhan and its province in the initial outbreak. Moreover, in Italy, news of hiring physicians from other countries like Cuba, China and Venezuela to support medical care of affected patients spread, since health systems were overwhelmed.

## **Research Question**

¿Does prophylactic treatment with hydroxychloroquine 200 mg/day for 60 days significantly reduce the incidence of symptomatic COVID-19 infections in healthcare workers in direct contact with infected patients compared with placebo?

## **Background**

The outbreak of respiratory infections due to coronavirus 2019 (COVID-19) began in China in December 2019, in the city of Wuhan, Hubei province (1 – 5). From this city, the outbreak has extended to other Chinese provinces and other countries (6). Until February 16, 2020, 28 countries had recognized confirmed cases, with 70,548 infections and 1,770 deaths in China and 413 infections in Japan (6). As other coronavirus, like SARS and MERS, the original human infection probably came from contact with animals, but effective transmission between humans has been proved, with a growth rate higher than 1 estimated at 2.6 (7) and a rapid duplication of cases that guarantees not only the continuation of the epidemics but its expansion, as has been observed so far.

COVID-19 has a wide range of clinical presentations, from asymptomatic infections to fatal disease with severe lung damage, respiratory failure and multiorgan failure. Severe damage has been associated, as in severe influenza, to a systemic

inflammatory reaction or cytokine storm, that may be attenuated by the immunomodulator effect of chloroquine or hydroxychloroquine. The fatality rate of COVID-19 has been estimated around 2%, but in severe cases with respiratory failure or need of intensive care it is considerably higher, between 10 – 15%, and could easily go up to 20 – 30% depending on the criteria of admission to an intensive respiratory care unit.

Until now there is no effective treatment for COVID-19 available, but it was recently reported that Remdesivir and chloroquine are effective in vitro. This one, in concentrations that can be obtained in vivo (8). Chloroquine and hydroxychloroquine (HCQ) are originally antimalarial drugs, almost identical chemically, that have been in regular use for decades, with a good security profile and accessible cost. The main toxicity of HCQ, investigational drug in this trial; is retinopathy, being its main associated risk factors doses higher than 5 mg/kg weight/day, lengthy use (longer than 10 years) and history of kidney failure, as well as use of tamoxifen. Other adverse effects reported with HCQ, happening scarcely, are alterations of heart conduction, cardiomyopathies, neurological symptoms such as nystagmus, headache, insomnia and nightmares, among others.

The antiviral effect of HCQ has been attributed to the increase in endosomal pH, being endosomes required for viral-cellular fusion, and to interference with glycosylation of the coronavirus (SARS-CoV-2) cellular receptors (9-11). Besides its antiviral effect HCQ also has immunomodulator effects, which are used for treatment of diseases like rheumatoid arthritis and systemic erythematosus lupus. This effect may enhance the antiviral effect and diminish the systemic impact of severe infection. In case of being effective as prophylaxis, it could be a very useful drug to lower the risk of COVID-19 in healthcare workers.

Recently a letter was published (12), describing how in February 17 the State Council of China had given a press announcement indicating that chloroquine had shown marked efficacy and acceptable security for the treatment of COVID-19 pneumonia in multicentric trials with more than 100 subjects in 10 hospitals. On the other hand, reports of therapeutic success using HCQ in combination with azithromycin have come out, which even being preliminary support the thesis of the antiviral effect of HCQ and its possible use as prophylaxis in subjects at risk of COVID-19. Based on the above, we propose this double blind randomized clinical trial, with two parallel groups, of treatment with HCQ against placebo, to evaluate the efficacy and security of HCQ in healthcare workers with risk of COVID-19.

## **Justification**

There is a lack of an approved pharmacologic treatment for chemoprophylaxis of COVID-19 and based on the in vitro effectivity of HCQ against the SARS-CoV-2 virus, its security profile and low cost we propose a randomized double blind controlled trial to evaluate the efficacy and security of HCQ to prevent symptomatic and severe infections in the healthcare workers highly exposed to COVID-19. The proposed dosage for prophylaxis is 200 mg/day. This is lower than 5 mg/kg/day in subjects who weight more than 50 kg, which makes the risk of retinal toxicity minimal, since subjects who weigh less than 50 kg will be excluded. In case of proving that the incidence of symptomatic and severe COVID-19 in health workers diminish significantly, this prophylaxis strategy may be one of the best tools to upkeep the security of the healthcare personnel exposed to COVID-19.

## **Hypothesis**

Alternate hypothesis: Prophylactic treatment with hydroxychloroquine 200 mg/day for 60 days reduces the incidence of symptomatic infections due to SARS-CoV-2 in more than 10% in healthcare workers in contact with infected patients.

Null hypothesis: Prophylactic treatment with hydroxychloroquine 200 mg/day for 60 days doesn't reduce the incidence of symptomatic infections due to SARS-CoV-2 in more than 10% in healthcare workers in contact with infected patients.

## **General objectives**

To evaluate the efficacy of prophylaxis with HCQ at a 200 mg/day dosage, compared against placebo, to diminish the incidence of symptomatic COVID-19 in healthcare workers with high COVID-19 exposure.

To evaluate the security of prophylaxis with HCQ at a 200 mg/day dosage, compared against placebo, to diminish the incidence of symptomatic COVID-19 in healthcare workers with high COVID-19 exposure.

### **Specific objectives**

To compare the risk of symptomatic infection with COVID-19 in subjects treated with prophylaxis with hydroxychloroquine against the risk of symptomatic infection with COVID-19 in subjects treated with placebo.

To estimate the risk of presenting the composite outcome (admission to intensive respiratory care unit, need of mechanical invasive /non-invasive ventilation and death) among subjects with high exposure to COVID-19, treated with prophylaxis with HCQ against those treated with placebo.

To estimate the risk of adverse effects in healthcare workers treated with prophylaxis with hydroxychloroquine against the risk of adverse effects in subjects treated with placebo.

### **Experimental design**

Clinical research.

Experimental, longitudinal, prospective study.

This study will obtain knowledge for the prevention of COVID-19.

The research line from which this project derives is the program of study about influenza and other respiratory viruses.

### **Material and Methods**

#### Place of study

Instituto Nacional de Enfermedades Respiratorias "Ismael Cosío Villegas" (National Institute of Respiratory Diseases, INER); areas of the Urgencies, Critical Medicine and Hospitalization Units.

#### Description of population

Healthcare workers from INER, in contact with the attention of COVID-19 patients, including medical personnel, nursing practitioners, and paramedics such as stretcher handlers and cleaning staff. The INER workers included will have taken training courses on the use of biosecurity protection, with the goal of lowering the risk of COVID-19 infection.

#### Procedures of the study

Phase III double blind controlled randomized trial, with two parallel groups.

#### *Randomization*

Healthcare workers exposed to patients with COVID-19 diagnosis will be distributed randomly in a stratified way. The strata for randomization will be the following:

- a) Group A: subjects with high-risk exposition to COVID-19; defined as the personnel who perform high risk invasive procedures (bronchoscopy, intubation, extubation and/or respiratory sample taking), care of critical or under mechanical ventilation patient.
- b) Group B: subjects with low to moderate risk exposition to COVID-19; defined as the personnel who attend patients in triage or outpatient areas, or whose participation in the Unit corresponds to cleaning or administration labour.

The randomization distribution will be performed with the permuted block method with random allocation, in blocks of four pairs.

### *Blind description*

Subject, researcher, treating physician, outcome monitor, results analysis.

### *Main outcome*

Symptomatic infection (dry cough with or without dyspnea, with or without fever) due to COVID-19 proved via PCR-TR according to the OMS protocol.

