### *Secondary outcomes*

1. Admission to the Intensive Respiratory Care Unit , need of invasive/non-invasive mechanical ventilation, death secondary to COVID-19, proved via PCR-TR according to the OMS protocol.
2. Incidence and severity of adverse events  
Adverse event: all medical events in the subjects included in the trial. The adverse event doesn't necessarily need to have a causal relation with the studied treatment. Examples of adverse events include abnormal symptoms and signs, hypersensitivity reactions or alterations in laboratory samples.  
Severe adverse event: defined as an event that results in the subject's death, in an event that threatens life, that requires hospital admission or causes incapacity.  
Due to the known effects of HCQ, special attention will be given to the incidence of the following adverse events:
  - a) Cutaneous reaction, generally when used along other drugs.
  - b) Medullar suppression, which must be watched over monthly through a control blood count.
  - c) Severe hypoglycemia, in which case the treatment must be suspended.
  - d) Proximal myopathy with proximal weakness or muscular atrophy.
  - e) Increase of suicidal risk according to the C-SSRS scale.

Adverse reactions are defined as the answer to a compound that is harmful and involuntary, that occurs at doses that normally are administrated to human beings. The described adverse reactions are:

- 1- 10% ophthalmologic, dose dependent.
- 2- Non-defined frequency: dermatologic, endocrine, metabolic, gastrointestinal, hematologic, hepatic, central nervous system, immunologic.

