### *Gradation of adverse reactions*

Grade 1: mild adverse event: refers to the effects that may happen due to the compound that are temporal and don't cause permanent harm or incapacity.

Grade 2: moderate adverse event; refers to the effects that may happen due to the compound that are temporal but require support from other therapeutics to be corrected and don't cause permanent harm or incapacity.

Grade 3: severe adverse event; refers to the effects that may happen due to the compound that might be temporal or permanent, without risk of mortality or incapacity.

Grade 4: adverse advent with risk of death or incapacity.

Evaluated through the following study:

Electrocardiogram: QT interval prolongation.

Blood count: bone medulla suppression, defined with the following values: neutrophiles < 500/microliters, platelets < 20,000/microliter, reticulocytes < 20,000 / microliter.

Hepatic failure: INR > 1.4, ALT > 33 units/liter, AST > 55 units/liter, total bilirubin > 4 mg/dl, platelets < 150,000/microliter.

Due to the nature of the study, having a captive population that comes to the INER at least five days a week, it is possible to estimate the number of days to the outcome. All participants will be instructed to notify the researchers in case of presenting cough, dyspnea or any other new sign or symptom. Weekly researchers will ask all included subjects about the symptoms associated with COVID-19, as well as any possible adverse events.

If any study subject presents adverse reactions, the treatment will begin immediately, and it will be notified at the same time. The initial treatment will be administered at the INER, support from other institutions will be requested, if necessary, without cost for the subject.

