#### *Ending of recruitment*

#### *Tests to perform*

- Minimum tests at recruitment (before randomization) and at 30 and 60 days:
  - Blood count
  - Serum electrolytes
  - Blood chemistry (3 elements): to quantify the effects on blood sugar and rule out type 2 diabetes mellitus at baseline.
  - Hepatic profile
  - Electrocardiogram: to evaluate the incidence of heart conduction alterations.
- 10-respiratory virus and SARS-CoV-2 panel, only in case of symptoms.

At 30 and 60 days: surveillance of adverse events.

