### Statistical analysis

Categorical variables will be described with frequencies and percentages, numerical variables with mean and standard deviation or median and interquartile range according to their distribution. The time to the outcome (COVID-19) and to the compound outcome will be estimated, in both the experimental and the placebo group. The survival function will be estimated with the Kaplan – Meier method and the log rank hypothesis test will be used to contrast the time to outcome in each study group. The hazard ratio and its 95% confidence interval will be used as measure of association strength to evaluate the effect of the prophylactic HCQ over the main and secondary outcomes of the study. The effect of prophylaxis on both proposed

study strata will be estimated with the log rank test, and the interaction prophylaxis – strata will be evaluated with Cox regression. Due to the urgency of knowing the study results, the following interim analysis are proposed: at the moment that the 50% of the sample has had a follow-up of four weeks and at the moment that 50% of the sample has had 8 weeks of follow-up. The subjects that do not present the outcome will be censored in their follow-up at three months from the random allocation and start of the intervention (HCQ/placebo). We propose a multivariate Cox analysis to evaluate the risks associated with COVID-19 and risk of the composite outcome. All analysis will be two-tailed, the analysis strategy is intention to treat, and all randomized subjects will be included in the analysis.

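### The main outcome makes dry cough mandatory, which is narrower than the symptomatic COVID-19 that the protocol asks about, plans for and analyses

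*Protocol*

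**What the plan says.** Protocol, Main outcome, defines the event as "Symptomatic infection (dry cough with or without dyspnea, with or without fever) due to COVID-19 proved via PCR-TR according to the OMS protocol". No other section restates or widens this definition.

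Elsewhere the concept is broader:

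- General objectives: the aim is "to diminish the incidence of symptomatic COVID-19 in healthcare workers with high COVID-19 exposure". Research Question and Hypothesis likewise speak of symptomatic infection, with no cough condition.
- Final calculation: the planning rate is a 76% survival rate free of COVID-19, with a 10-point improvement.
- Statistical analysis: "The time to the outcome (COVID-19) and to the compound outcome will be estimated", and "The subjects that do not present the outcome will be censored in their follow-up at three months from the random allocation".
- Follow-up paragraph under Gradation of adverse reactions: "All participants will be instructed to notify the researchers in case of presenting cough, dyspnea or any other new sign or symptom". Separately, researchers ask every subject weekly about COVID-19 symptoms.
- Tests to perform: "10-respiratory virus and SARS-CoV-2 panel, only in case of symptoms". Which symptoms count is not stated.
- Secondary outcomes: intensive care admission, "need of invasive/non-invasive mechanical ventilation, death secondary to COVID-19, proved via PCR-TR". This composite has no cough requirement and is not part of the main outcome.

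**The concern.** In the main outcome's parenthesis, dry cough is the one element not qualified as optional, and nothing marks it as an example. A worker with PCR-proved infection, fever and dyspnea but no dry cough therefore does not meet the definition, although the trial's question plainly covers that worker.

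Two things are at stake. First, the primary estimate would describe dry-cough COVID-19, while the conclusion would be stated for symptomatic COVID-19. The interim look for efficacy described under the data and security monitoring committee uses the main outcome, so an early decision would inherit the mismatch. Second, the planning rate carries no cough condition. If some confirmed symptomatic cases do not qualify, the trial will have fewer primary events than it planned on.

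**Working it through.** **Reading the text**

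1. The event needs three things: PCR proof, symptoms, and dry cough among them. Dyspnea and fever may be present or absent.
2. A subject who does not present the outcome is censored at three months. A confirmed case without dry cough therefore stays in the primary analysis as event-free.
3. If that case is severe, it enters the secondary composite, for which time to event and a hazard ratio are also planned. It is a non-event for the primary analysis only.
4. The question, hypothesis, objectives, planning rate and analysis text all omit the cough condition. The mismatch is between the definition and the rest of the protocol.

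**Size, as an illustration**

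Inputs from the protocol: COVID-19-free survival 76% v 86% (Final calculation), 200 per arm (Final calculation), two-sided 5% (Significance level), 90% power (Power).

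The plan's own figure: the hazard ratio is ln 0.86 / ln 0.76 = 0.55, with |ln HR| = 0.5986. For 90% power the log-rank test needs 118 events (Schoenfeld) or 125 (Freedman). Dividing by 2 - 0.76 - 0.86 = 0.38 gives 311 or 329 per arm, so the stated 159 is not reproduced. That is a separate issue and is not evidence on this point.

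Baseline if every symptomatic case counts and nobody is lost: events = 200 × (0.24 + 0.14) = 76. Power = Φ(√(76/4) × 0.5986 - 1.96) = 74%.

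Let f be the share of symptomatic confirmed cases with dry cough. The protocol gives no value, so f is assumed, and assumed equal in both arms. Events become 76f and power becomes Φ(√(76f/4) × 0.5986 - 1.96).

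| Assumed f | Events | Power, HR held at 0.55 (Schoenfeld) | Power, HR recomputed from thinned rates (Schoenfeld) | Same, Freedman |
|---|---|---|---|---|
| 1.0 | 76 | 74% | 74% | 72% |
| 0.9 | 68 | 70% | 69% | 66% |
| 0.8 | 61 | 65% | 63% | 60% |
| 0.7 | 53 | 59% | 56% | 54% |
| 0.6 | 46 | 52% | 49% | 47% |

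The recomputed columns multiply both 24% and 14% by f, which moves the hazard ratio slightly, from 0.55 to 0.56 at f = 0.6. The pattern is the same whichever method is used.

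The 76 events use all 200 per arm, although the protocol raised 159 to 200 to cover losses. With 159 per arm the baseline is 318 × 0.19 = 60 events and 64% power, before any effect of the cough condition.

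**The case against.** The strongest reply is that the parenthesis is a loose description of symptomatic illness in a text that reads as a translation, and that the analysis section simply names the outcome COVID-19. That may have been the intent. But the definition contains no words such as for example, it is the only one given, and blinded assessors would have to apply it. If examples were meant, the wording still needs correcting.

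Several stronger readings are tempting and the document does not support them:

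- A reader might infer that confirmed cases without cough will certainly be detected and then discarded. The panel is done in case of symptoms, but which symptoms is not said. If the trigger follows the main-outcome wording, such subjects may never be tested. Nor is there a formal questionnaire: unscheduled notification by participants and weekly questioning by researchers are two separate mechanisms.
- A reader might infer that severe cases are lost to the trial. They are not; the secondary composite captures them. The protocol also gives no frequency for severe cases without dry cough.
- A reader might infer that hydroxychloroquine suppresses cough more than infection and so would bias the result. Nothing in the protocol says so.
- A reader might take the power loss as known. It rests wholly on the assumed share. It also supposes that the 76% rate includes cases without cough, and the protocol does not explain how that rate was defined.

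One objection stands in full. A definition anchored on cough has some protection against symptoms caused by the drug. The protocol lists headache and insomnia in its Background, and gastrointestinal and central nervous system reactions under Secondary outcomes, as effects of hydroxychloroquine. An endpoint open to any new symptom could prompt more testing, and so more detected infections, in the active arm. The fix has to respect this.

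**Conclusion.** The point holds as a mismatch between the stated event definition and the trial's own question, planning rate and analysis text. Applied as written, PCR-confirmed symptomatic COVID-19 without dry cough is a primary non-event. Severe cases without cough count in the secondary composite only.

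The size cannot be fixed from the protocol. On an assumed dry-cough share of 90% to 60%, equal in both arms, with 76 events at baseline and no losses, events fall to 68-46 and power falls by about 4 to 22 percentage points, from about 74% to 70-52%. The shortfall from the stated 90% to 74% does not come from the cough condition. The mismatch itself needs no assumption about the share. It should be corrected, because it is a stated rule for the primary event and not a detail that could be left to the statistical analysis plan.

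**What to change.** Reword the main outcome as PCR-confirmed SARS-CoV-2 infection with at least one symptom from a prespecified list of COVID-19 symptoms, at minimum cough, dyspnea or fever, or with intensive care admission, ventilation or death due to COVID-19. State in Tests to perform that the same list triggers PCR in both arms. Keep the dry-cough definition as a sensitivity analysis. In Final calculation, say which event definition the 76% rate refers to.

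The cost is mainly wording, since symptom surveillance and symptom-triggered PCR are already planned, but the symptom list does not yet exist and has to be written. It should not rely on non-specific symptoms that are also listed effects of hydroxychloroquine, such as headache or gastrointestinal complaints, because these could lead to different testing rates between the arms.
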